### Outcome measurements

A blinded assessor will perform tests of foot mobility and other outcome measurements at baseline and then at follow-up sessions occurring at 1, 2, and 6 weeks. Participants will also be contacted by email or phone to obtain questionnaire outcome measurements only at 12, 18, 24 and 30 weeks. At the completion of the test sessions, assessor blinding will be evaluated via a questionnaire.

Biomechanical effectiveness of the intervention will be evaluated by measuring vertical mobility of the midfoot. These measures will be performed at baseline and then at follow-up sessions occurring at 1, 2, and 6 weeks. In addition to these measurements by the assessor, the treating physiotherapist will also obtain a measurement of foot mobility before and after each application of tape to ensure consistency of application of the intervention. Measurement of vertical mobility of the midfoot will be performed using two custom made platforms and modified callipers with the participant in two positions (i) standing on both feet with equal weightbearing and, (ii) sitting with legs relaxed over the edge of a plinth. Dorsal arch height difference will be calculated by subtracting the dorsal arch height in standing from the dorsal arch height in non-weight bearing. This measurement has been described in detail previously and demonstrates high inter- and intra-rater reliability [15].

#### Visual Analogue Scale

Usual and worst pain over the preceding week will be obtained using two separate 100 mm visual analogue scales (VAS). The reliability and validity of the VAS is well established [27]. Each VAS will consist of a 100 mm horizontal line with the text ‘no pain’ at the 0 mm mark and ‘worst pain imaginable’ at the 100 mm mark. Participants will be instructed to place a single vertical mark on the horizontal line that represents the level of their pain.

#### Foot and Ankle Ability Measure

Function will be measured using the Foot and Ankle Ability Measure (FAAM) which provides an indication of participation in usual activities [28]. The FAAM is a set of eight (8) items that are each scored by the participant from 4 to 0, with a score of 4 indicating no difficulty with the functional task and 0 indicating that the participant is unable to perform the task. Thus, the greater the FAAM score, the higher the level of function. The validity, reliability and responsiveness of the FAAM has been previously demonstrated [28].

#### Patient Specific Functional Scale

The Patient Specific Functional Scale (PSFS) provides a method for eliciting, measuring and recording descriptions of patients’ disabilities that are most relevant to them. Participants will be asked to identify up to five (5) important activities that they are having difficulty with or are unable to perform. The current level of difficulty associated with each activity is then marked on an 11-point scale, where 0 is ‘unable to perform activity’ and 10 is ‘able to perform activity at the same level as before the injury or problem’. This scale has been shown to have excellent test-retest reliability, sensitivity to change, and validity [29].

#### Global perceived effect

Global perceived effect will be measured with a 6-point Likert scale with categories: completely recovered, much improved, improved, no change, worse and much worse. Such retrospective assessment scales have been shown to be more sensitive to change and more correlated with patient’s satisfaction with change than serial assessment scales that include a baseline measurement, such as the VAS [30]. This outcome measure will be performed at each of the follow-up sessions, but not at baseline.

#### Amount of activity performed in the previous week

The physical activity level of participants will be quantified using a physical activity questionnaire which has previously demonstrated moderate to high reliability [31]. The participant will record the amount of time spent in occupational, household, and leisure activities of ‘moderate’, ‘hard’ and ‘very hard’ intensities during the previous week. The total time for each intensity level of activity is then multiplied by the metabolic equivalents of the activities and summed to give an overall caloric output. This can then be standardised to body weight to allow comparison between and within individuals over time.

A further questionnaire regarding any adverse responses and perception of comfort of the taping interventions, as well as whether participants have sought any treatment outside the study, will be administered at follow-up sessions at 1, 2 and 6 weeks.

### Sample size considerations

Sample size calculations [32] indicate that 10 participants per group will be sufficient to detect (i) a clinically significant improvement of 20 mm in pain severity [33] based on a standard deviation of 12.7 mm [34], power of 0.80 and alpha level 0.05 and (ii) a clinically significant improvement of 9 points [28] on the FAAM based on a standard deviation of 26.7 [28], power of 0.80 and alpha level of 0.05. To account for potential dropout, 15 participants per group will be recruited, with a total sample size of 45.

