**Methods/Design:**

A single-blinded randomised controlled clinical trial will be conducted in a community setting. Forty-five female volunteers aged between 18 and 40 years with a history of insidious onset of pain located between the knee and ankle of at least one month duration that is aggravated by weight bearing activities will be recruited for the study. Suitable participants will be randomly allocated to one of three treatment groups for the 6 week intervention period: (i) exercise only, (ii) rigid anti-pronation tape and exercise, (iii) elastic anti-pronation tape and exercise. Outcomes will be measured at baseline, 1, 2 and 6 weeks using primary outcome measures of usual and worst pain visual analogue scale and global perceived improvement. Secondary outcome measures will include Foot and Ankle Ability Measure, Patient Specific Functional Scale and amount of activity in the previous week. In addition, participants will be contacted by phone to obtain primary and secondary outcome measures at 12, 18, 24 and 30 weeks.

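### The stated 80% power for the FAAM does not follow from its own inputs: 10 per group with 9 points and SD 26.7 gives about 11%

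*Protocol article*

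**What the plan says.** Under 'Sample size considerations' the protocol article states that "10 participants per group will be sufficient to detect" two effects. The first is "a clinically significant improvement of 20 mm in pain severity [33] based on a standard deviation of 12.7 mm [34"]. The second is an "improvement of 9 points [28] on the FAAM based on a standard deviation of 26.7 [28], power of 0.80", with the same alpha of 0.05. To allow for dropout, "15 participants per group will be recruited, with a total sample size of 45". No test, sidedness or correlation between sessions is given.

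Under 'Foot and Ankle Ability Measure' the instrument is described thus: "The FAAM is a set of eight (8) items that are each scored by the participant from 4 to 0". Higher scores mean better function. No total range and no conversion to a percentage is stated.

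The Abstract places the measure among the secondary outcomes: "Secondary outcome measures will include Foot and Ankle Ability Measure". 'Planned statistical analysis' specifies a group-by-session repeated-measures ANOVA for it. The 'Discussion' says that if the three groups do not differ, taping would be regarded as adding nothing to exercise.

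**The concern.** One sentence assigns the same group size, power and alpha to two standardised effects that differ almost fivefold: 20/12.7 = 1.57 for pain and 9/26.7 = 0.34 for the FAAM. Both statements cannot be right under one method of calculation.

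The consequence lies in how a null result is read. The Discussion already says what a finding of no difference would mean for taping. A reader who believes that the FAAM comparison had 80% power would count a non-significant FAAM result as support for that conclusion. At about 11% power, a true 9-point difference would be missed about 89% of the time, so such a result would say very little.

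The planning figures also do not sit with the score as described. A raw sum of eight items scored 0 to 4 runs from 0 to 32, and an SD of 26.7 is too large for that range.

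**Working it through.** **Inputs**, all from 'Sample size considerations' unless noted: 10 per group evaluable, 15 per group recruited; VAS difference 20 mm, SD 12.7 mm; FAAM difference 9 points, SD 26.7; power 0.80; alpha 0.05. Three groups (Abstract). FAAM items: eight, scored 0 to 4 ('Foot and Ankle Ability Measure'). Two-sided testing and a two-sample t-test are assumptions, since neither is stated; the alternatives are tried in step 3.

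**1. The VAS statement is reproduced.** d = 20/12.7 = 1.575. The normal approximation n = 2(1.96 + 0.842)²/d² gives 6.3, so 7 per group. With the noncentral t, 8 per group gives 83% and 10 gives 91%. The claim that 10 suffice is correct.

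**2. The FAAM statement is not.** d = 9/26.7 = 0.337.
- At 10 per group: noncentrality 0.337 × √(10/2) = 0.754 against a critical t of 2.101 (18 df); power 11.0% (11.4% by normal approximation).
- At 15 per group: noncentrality 0.337 × √(15/2) = 0.923 against 2.048 (28 df); power 14.5%.
- For 80% power: 2(1.96 + 0.842)²/0.337² = 138.2, so 139 per group, or 140 with the t distribution.
- Difference detectable with 80% power: about 35 points at 10 per group and 28 at 15. For 9 points to be detectable at 10 per group, the SD would have to be about 6.8.

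**3. Other readings that use only the printed inputs, at 10 per group:**

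| Reading | Power | n per group for 80% |
|---|---|---|
| Two-sample, two-sided | 11.0% | 140 |
| Two-sample, one-sided | 17.9% | 110 |
| Paired within group (26.7 taken as SD of change) | 15.9% | 72 |
| Three-group F test, one group 9 points apart | 10.5% | 129 |

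**4. Readings that need an assumed correlation r, at 10 per group:**
- ANCOVA on one follow-up, variance factor 1 − r²: 13%, 17% and 37% at r = 0.5, 0.7 and 0.9; about r = 0.97 is needed for 80%.
- Mean of all seven follow-ups with baseline adjustment, variance factor (1 + 6r)/7 − r²: 24% at r = 0.5 and 38% at r = 0.8; 80% at about r = 0.94.
- Group-by-session interaction with effect size f = d/2: 86% with 4 sessions at r = 0.8, and 87% with 8 sessions at r = 0.7. This convention is optimistic. If instead one group is 9 points better at every follow-up and equal at baseline, interaction power is about 8% to 35% for r = 0.5 to 0.9 with 4 or 8 sessions.
- Group main effect in the repeated-measures model: about 11% to 20% for r = 0.3 to 0.9.

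**5. Scale.** The raw total runs from 0 to 8 × 4 = 32. The largest SD on that range, with half the scores at each end, is 16 (16 × √(10/9) = 16.9 as a sample SD with 10 observations). An SD of 26.7 is therefore impossible on it; a 9-point difference is possible. On a 0–100 score both figures are possible. Converting both to raw points gives 9 × 0.32 = 2.88 and 26.7 × 0.32 = 8.54, the same d of 0.337 and the same 11%. Even the mixed reading, 9 raw points (9/32 = 28.1%) against an SD of 26.7%, gives 61%.

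**The case against.** The strongest reply is that no test is named and a repeated-measures ANOVA is planned, so the authors may have used software for that design. This stands in part: as step 4 shows, an interaction calculation with correlations of roughly 0.7 to 0.8 can print a figure above 80%. But the article gives no correlation, number of sessions or interaction effect, and that convention is generous to a sustained 9-point benefit. As printed, the claim remains unsupported.

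A second reply is that the FAAM is secondary and the VAS justification is sound. This stands, and it limits the point to a wrong power statement.

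A third is that a condensed article may leave the scoring of a published instrument to its source, and that the text never says a raw sum is analysed. This also stands. The scale question is a request for clarification.

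A reader might infer more than the documents support:
- that the FAAM is the main function outcome: the article lists it beside the Patient Specific Functional Scale and ranks neither above the other;
- that the VAS answer was simply copied across to the FAAM: nothing in the text shows how the error arose;
- that the 20 mm and 9 points were used as differences between arms: the section speaks only of improvement and names no comparison;
- that the clinical benchmark is wrong about threefold: this would follow only if a raw 0–32 score were analysed against 9 points, which the article does not say.

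**Conclusion.** The FAAM power claim is wrong as written. From the printed difference, SD and alpha, power is about 11% at 10 per group and 14.5% at 15, not 80%, and about 140 per group would be needed. These figures assume a two-sided two-sample t-test; the other readings that need no further input stay at or below 18%. Reaching 80% needs a high between-session correlation that the article does not state. The error does not touch the VAS calculation or the total of 45. It matters because the Discussion would interpret an absence of difference as an absence of benefit from taping. The SD of 26.7 also cannot belong to a raw 0–32 total, so the planning figures appear to be on another scale, presumably 0–100; this does not change the power.

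**What to change.** In 'Sample size considerations', delete the FAAM claim, or restate it along these lines: with 10 to 15 per group, power for a 9-point FAAM difference is about 11% to 15%, and the difference detectable with 80% power is about 28 to 35 points (35 at 10 per group, 28 at 15). Say that the sample size rests on the VAS alone. If a repeated-measures calculation lies behind the claim, restate it with the test, the number of sessions and the assumed correlation.

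In 'Foot and Ankle Ability Measure', state the scoring range that matches the planning figures.

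The cost is wording only, with no extra participants. The one drawback is a less favourable stated power for a secondary outcome.

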### Planned statistical analysis

Data processing, data entry and data analysis will be performed by an assessor who is blinded to group allocation. The primary analysis of the data will be performed on an intention-to-treat basis. SPSS software (version 21.0) will be used for statistical procedures. Demographic data, clinical characteristics of pain and physical activity level at baseline will be examined for comparability across the three intervention groups. To evaluate the effect of the interventions on pain and function (VAS, FAAM, PSFS, Physical activity level) a two-way repeated measure analysis of variance with between subject factor of intervention group and within subject factor of test session, will be performed. Global perceived effect will be dichotomised to either success (completely recovered, much improved, improved) or no success (no change, worse, much worse) and expressed as relative risk reduction and numbers needed to treat. For all statistical procedures age, weight and height will be included as covariates and alpha level will be set at 0.05.

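### For the two VAS primary outcomes, the named repeated-measures ANOVA keeps only women with complete sessions unless values are imputed first, which conflicts with the stated intention-to-treat basis

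*Protocol article*

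**What the plan says.** Three statements in the protocol article bear on this point.

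- **Population.** Under Planned statistical analysis: "The primary analysis of the data will be performed on an intention-to-treat basis".
- **Method.** The same section fixes the software, "SPSS software (version 21.0) will be used for statistical procedures", and the model for the VAS, FAAM, PSFS and physical activity level: "a two-way repeated measure analysis of variance with between subject factor of intervention group and within subject factor of test session". It adds: "For all statistical procedures age, weight and height will be included as covariates and alpha level will be set at 0.05".
- **Expected loss.** Sample size considerations finds 10 per group sufficient and then says: "To account for potential dropout, 15 participants per group will be recruited", which gives 45 in total.

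The abstract describes the trial as "using primary outcome measures of usual and worst pain visual analogue scale and global perceived improvement", so two of the three primary outcomes go through the ANOVA. The third does not: "Global perceived effect will be dichotomised to either success" or no success, and it is then reported as a relative risk reduction and a number needed to treat.

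On timing, the abstract says "Outcomes will be measured at baseline, 1, 2 and 6 weeks", with remote contacts at 12, 18, 24 and 30 weeks. That makes four clinic sessions and eight time points in all. The article does not say which of these are levels of the test-session factor. It mentions neither imputation nor a model that accepts incomplete rows.

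**The concern.** A classical two-way repeated-measures ANOVA works on one complete row per participant. A woman with a gap at any level of the within-subject factor contributes nothing, not even her observed values. The plan declares one population (everyone randomised) and names a method that, run as written, analyses another (those with complete rows). Its own dropout allowance shows that gaps are expected.

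Two things are at stake. First, if women in more pain stop responding more often, a comparison among those with complete rows can be biased. Under the mechanism examined below, the bias shrinks the difference between groups. That direction matters because the Discussion says a finding of no difference would lead to recommending exercise without tape. Second, observed early data can be thrown away. Tape is worn only in weeks 1 and 2, so those sessions carry the most direct information on taping.

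**Working it through.** **1. The plan's own allowance.** Inputs from Sample size considerations: 10 per group needed, 15 recruited. The allowance is 5/15 = one third. Check: 10 / (1 − 1/3) = 15 per group, and 3 × 15 = 45, which matches the stated total. If that allowance is used up and nothing is imputed, the ANOVA analyses 3 × 10 = 30 of 45 women.

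**2. Dependence on the sessions in the factor.** Assume baseline is complete and each follow-up is missed independently with probability m (m is not in the documents). The expected number of complete rows is 45 × (1 − m)^k, with k = 3 follow-ups for the four clinic sessions and k = 7 for all eight time points.

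| m (assumed) | Four sessions | Eight sessions |
|---|---|---|
| 2% | 42.4 | 39.1 |
| 5% | 38.6 | 31.4 |
| 10% | 32.8 | 21.5 |
| 15% | 27.6 | 14.4 |

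The miss rate that removes one third of the women is 1 − (2/3)^(1/7) = 5.6% per follow-up over eight sessions, and 1 − (2/3)^(1/3) = 12.6% over four.

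**3. Power.** Inputs from the same section: 20 mm, SD 12.7 mm, alpha 0.05 (taken as two-sided; the article does not say). The standardised difference is 20/12.7 = 1.575. Two-sample t-test power is 98.6% at 15 per group, 91.4% at 10 and 77.2% at 7. Going from 15 to 10 per group widens standard errors by √(15/10) = 1.22, but the trial keeps its planned power at 10 per group.

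**4. Bias, as an illustration.** A large-sample simulation assumed a true 20 mm benefit at all follow-ups. One third of women dropped out after week 6, with a probability depending on observed week-6 pain (logistic slope 0.05 to 0.10 per mm). SD was 12.7 to 20 mm and the between-session correlation 0.5 to 0.7. Only the 20 mm, the SD of 12.7 mm and the one third come from the article. Among women with complete rows, the arm difference in week-6 change from baseline was 17.0 to 19.6 mm. The bias is therefore 20 − 19.6 = 0.4 mm to 20 − 17.0 = 3.0 mm towards no effect. This applies only if later sessions sit in the same model as week 6.

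**The case against.** The strongest reply is that the article is a condensed document. Imputation and the definition of the intention-to-treat set are commonly left to the full protocol or analysis plan, and nothing in the article says incomplete participants will be excluded. That stands in part. A reader might infer that the primary analysis will certainly be completers-only. The documents do not support that, because imputation before the ANOVA would avoid it. What remains is that the article does not leave the model open. It names one that, taken as written, does not deliver the population it declares.

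Other stronger readings also fail:

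- **One missed 18-week call erases a woman's weeks 1 to 6.** This is true only if all eight time points are in one factor. Outcome measurements uses session language for weeks 1, 2 and 6 and describes the later contacts separately, so a four-session factor is a fair reading. On that reading, dropout after week 6 removes nobody from the analysis of weeks 0 to 6.
- **The effect shrinks to 14 to 18.5 mm.** The same simulation gives that range for the raw week-6 difference. The group-by-session effect, with baseline as a session, concerns change, where the bias is smaller.
- **The trial loses its power.** It was sized on 10 per group, and 15 is a cushion rather than a forecast of one-third attrition.
- **Every primary outcome is affected.** Global perceived effect is outside the ANOVA.
- **SPSS is at fault.** Deletion belongs to the classical repeated-measures routine; the same software fits mixed models.
- **Unequally spaced sessions break the method.** Session is a categorical factor, so unequal spacing is not in itself a defect.

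**Conclusion.** The concern holds in a conditional form. For usual and worst pain VAS, and for FAAM, PSFS and physical activity, the named ANOVA analyses only women with complete rows unless missing values are imputed first. At the plan's own allowance that could be 30 of 45, which does not fit an intention-to-treat analysis.

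The actual loss depends on an unstated choice of sessions. At an assumed 5% independent miss rate it leaves about 39 complete women with four sessions and 31 with eight. The conflict exists on either reading; only its size changes.

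The main cost is possible bias, 0.4 to 3 mm of 20 mm on change from baseline. That figure rests on assumed dropout mechanisms and on all sessions being in one model. The loss of observed early data comes second, and power is a minor issue. Because two of three primary outcomes are involved and the remedy is cheap, it should be settled before unblinding.

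**What to change.** Replace the repeated-measures ANOVA with a likelihood-based linear mixed model for repeated measures (SPSS MIXED), specified as follows:

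- All randomised women enter with all their available data. If baseline is kept as a level of session, a woman seen only at baseline still contributes.
- Session is categorical, with group, session and their interaction, and results are reported as group-by-session contrasts.
- Age, weight and height stay as covariates, as planned.
- The sessions in the model are listed.
- The covariance structure is named in advance and is simple enough for 45 participants. An unstructured matrix has 4 × 5 / 2 = 10 parameters for four sessions but 8 × 9 / 2 = 36 for eight.

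If the ANOVA is kept, state the imputation that precedes it.

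The cost is a change of analysis wording, with the same data and software. There is a small downside: a covariance structure has to be chosen, and the mixed model is valid only if data are missing at random given what was observed. It would not correct for dropout driven by pain that was never recorded.

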### Recruitment of participants

Female volunteers will be recruited from paid advertisements in local community newspapers, supplemented by regular postings of advertisements on noticeboards within the University and wider community (e.g. gymnasiums, sporting clubs, health clinics). Each potential participant who responds to advertisements will undergo a screening process (via phone or email) to determine eligibility. Eligible volunteers will be provided with an information sheet thoroughly explaining the study and informed written consent to participate in the study will be obtained. Once eligibility has been determined and the informed consent process completed, participants will be assigned an identification number. Enrolled participants will attend a baseline testing session at which an assessor blinded to group allocation will obtain demographic information (age, weight, height), clinical characteristics of ERLP (nature, location, duration, onset, previous treatment), exercise history (intensity, duration and modality of current participation, and participation prior to the onset of ERLP), and perform outcome measurements. At the conclusion of baseline outcome measurements, the participant will be notified of group allocation by the treating physiotherapist and the intervention will commence.

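### The analysis of pain, function and activity adjusts for age, weight and height but not for the baseline value of the outcome, which gives up precision but not validity

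*Protocol article*

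**What the plan says.** The Planned statistical analysis section of the protocol article sets out, for VAS, FAAM, PSFS and physical activity level, "a two-way repeated measure analysis of variance with between subject factor of intervention group and within subject factor of test session". It then gives one covariate rule: "For all statistical procedures age, weight and height will be included as covariates". The section's only other stated use of baseline data is a check that the three groups are comparable.

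The Outcome measurements section has a blinded assessor take "outcome measurements at baseline and then at follow-up sessions occurring at 1, 2, and 6 weeks", with questionnaires added at 12, 18, 24 and 30 weeks. The Recruitment of participants section fixes the order of events: "At the conclusion of baseline outcome measurements, the participant will be notified of group allocation by the treating physiotherapist". That section also calls the baseline visit a testing session, but the analysis section does not list which sessions form the within-subject factor.

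Global perceived effect stands apart: "This outcome measure will be performed at each of the follow-up sessions, but not at baseline".

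**The concern.** The baseline value of an outcome is usually among the best available predictors of its later value. Here it is recorded before the participant learns her group, so it is a legitimate covariate. The plan instead adjusts for three demographic and body-size variables.

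The trial is small: 15 recruited per group, with 10 per group treated as sufficient in the Sample size considerations section. Chance differences in baseline pain between groups of that size are not negligible, and neither a change comparison nor a follow-up-only comparison handles them well. The Discussion intends to read an absence of group differences as showing that taping adds nothing to exercise. A less precise comparison makes that conclusion easier to reach by chance.

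**Working it through.** **Inputs.** From the Sample size considerations section: 20 mm and SD 12.7 mm for VAS; 9 points and SD 26.7 for FAAM; power 0.80; alpha 0.05; 10 per group, 15 recruited. From the Outcome measurements section: four assessed sessions, or eight with the later questionnaires. The documents give no correlation *r* between baseline and follow-up, so *r* = 0.3, 0.5 and 0.7 are assumptions. Whether the stated SDs are for raw scores is not said; raw scores are assumed.

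**The plan's own figure.** There is none for this point; the nearest is the VAS sample size. Two groups, two-sided: 2 × (1.960 + 0.842)² × (12.7/20)² = 6.3, so 7 per group (8 by the t distribution). The stated 10 covers this.

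**Reading A: baseline is a level of test session.**

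1. *Group main effect.* A constant post-baseline effect τ is averaged with one session at zero: 3τ/4 with four sessions, 7τ/8 with eight.
2. *Group by session.* A contrast of one follow-up with baseline is a comparison of change. With equal SDs *s*, its variance per participant is 2*s*²(1 − *r*). With baseline adjustment it is *s*²(1 − *r*²). The ratio is (1 + *r*)/2.

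**Reading B: baseline is not a level.** The contrast is follow-up only, with variance *s*². The ratio for baseline adjustment is 1 − *r*².

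| Assumed *r* | Adjusted / change (A) | Adjusted / follow-up only (B) |
|---|---|---|
| 0.3 | 0.65 | 0.91 |
| 0.5 | 0.75 | 0.75 |
| 0.7 | 0.85 | 0.51 |

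**Unequal SDs.** Let *k* be the baseline SD divided by the follow-up SD, with follow-up SD 1. Change has variance *k*² + 1 − 2*kr*, and the adjusted contrast 1 − *r*². The difference is (*k* − *r*)², which is never negative. The Eligibility criteria require worst pain of at least 30 mm, which may narrow the baseline. At *k* = 0.7 (assumed) the change variance is 1.07, 0.79 and 0.51 at the three correlations, and the ratios are 0.91/1.07 = 0.85, 0.75/0.79 = 0.95 and 0.51/0.51 = 1.00.

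**Chance imbalance.** The standard error of a baseline difference between two groups is SD × √(2/n). Taking 12.7 mm as the baseline SD (an assumption), this is 4.6 mm at n = 15 and 5.7 mm at n = 10. With equal SDs, a baseline difference D leaves an error of (1 − *r*)D in the change comparison and *r*D in follow-up only. At *r* = 0.5 and D = 4.6 mm both are 2.3 mm, against a target of 20 mm.

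**Effect on power at the protocol's own figures.** Two groups, one follow-up, normal approximation, change to baseline-adjusted:

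- VAS, n = 10: 84.5% to 95.8% at *r* = 0.3; 94.1% to 98.2% at *r* = 0.5; 99.5% to 99.9% at *r* = 0.7.
- VAS, n = 15, *r* = 0.5: 99.1% to 99.9%.
- FAAM, n = 15, *r* = 0.5: 15.0% to 18.6%.

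**The case against.** The strongest reply has four parts.

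*The session levels are inferred.* This stands. The dilution of the main effect and the (1 + *r*)/2 ratio belong to Reading A only. The lack of baseline adjustment holds under both readings.

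*The ratios are not those of the planned test.* This also stands. They describe a single contrast, whereas the interaction is an omnibus test with (3 − 1) × (4 − 1) = 6 numerator degrees of freedom for four sessions, or 2 × 7 = 14 for eight. A reader might infer from 0.75 at *r* = 0.5 that the planned test needs one third more participants (1/0.75 = 1.33). The documents do not support that: they name no such contrast, give no correlation and do not establish equal SDs. Nor does the plan name the group main effect as the treatment test, so a reader should not take the 3/4 or 7/8 dilution as the loss in the main result. The interaction does use baseline, so under Reading A the loss is partial.

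*Nothing is invalid.* Correct. Under random allocation the unadjusted comparisons are unbiased over repeated allocations, and omitting baseline does not inflate type I error. It would be wrong to infer a biased analysis.

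*The practical gain may be small.* At 20 mm and SD 12.7 mm, power is already high in most of the cases shown. For FAAM, adjustment does not rescue a comparison that is far short of power for a separate reason: the same sample size formula gives 139 per group. The gain matters more for VAS effects below 20 mm, with a low correlation, or with losses down to 10 per group.

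**Conclusion.** The point holds as a loss of precision. The protocol states its covariate rule for all procedures and omits the baseline value of VAS, FAAM, PSFS and activity, although these values are at hand. In large samples baseline adjustment is never less precise than change or follow-up alone. In this trial it costs one residual degree of freedom: with three groups and three covariates, 45 − 6 = 39 falls to 38.

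The size is not fixed by the documents. For one contrast with equal SDs and *r* between 0.3 and 0.7, the variance falls by 15% to 35% against change, or by 9% to 49% against follow-up alone. The gain over change shrinks, possibly to nothing, if the entry floor narrows the baseline SD of worst pain; it grows if follow-up scores vary less than baseline scores. These figures do not carry over directly to the omnibus interaction. The change is worth making because it is cheap, not because the planned analysis is unsound.

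**What to change.** For VAS, FAAM, PSFS and physical activity, do one of the following:

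- use follow-up sessions only as the within-subject factor, with the baseline value of the same outcome as a covariate together with its interaction with session; or
- fit a mixed model that keeps baseline as a response with one mean common to all three groups.

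List the sessions that enter the model, and state the choice before unblinding so that it cannot be seen as a post hoc selection of covariates. Age, weight and height may stay if wanted. Leave global perceived effect as planned, since it has no baseline value.

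The cost is a few lines of analysis text covering the factor levels, the covariate and its session term. No new data, visits or participants are needed.
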